#### Secondary outcomes

The secondary outcomes measured are static and dynamic postural balance, fear of falling, muscle strength and endurance (peripheral and respiratory), functional capacity, HRQoL, muscle architecture (quadriceps and diaphragm) and laboratory biomarkers.

##### Static postural balance

To assess vestibular, proprioceptive, and visual functions, dynamic flow-laser posturography will be used. Each evaluation will be performed three times for 20 seconds and considering for analysis the mean of the values obtained [19].

##### Dynamic postural balance

Dynamic postural balance will be assessed using the Timed Up and Go (TUG). Three tests will be performed and the best result one will be considered [20].

##### Static and dynamic postural balance

The Berg Balance Scale and the Balance Evaluation Systems Test (BESTest) will be also used to assess the static and dynamic postural balance [21, 22].

##### Assessment of fear of falling

The fear of falling will be assessed using the Falls Efficacy Scale-International-Brazil (FES-I-Brazil) [23] and the Activities-specific Balance Confidence (ABC) scale [24].

##### Respiratory muscle strength

The evaluation of respiratory muscle strength will be performed by means of measurements of maximal inspiratory pressure (MIP) and maximal expiratory pressure (MEP) with an MVD 300 digital manometer (MDI^®^, RS, BR). The highest pressure of MIP and MEP will be considered [25].

##### Inspiratory muscle endurance

The assessment of inspiratory muscle endurance will be performed by using POWERbreathe^®^ Medic Plus (POWERbreathe Medic Plus®, SP, BR), coupled to an analogical pressure transducer (WIKA, Alexander Wiegand SE & Co., Klingenberg, Germany). The evaluation will be composed of the incremental and constant tests [25].

##### Peripheral muscle strength

The assessment of upper limb muscle strength will be performed by a hydraulic dynamometer (Saehan Corporation SH5001, Korea) and the highest value obtained in each limb considered for analysis [26]. Lower limb muscle strength will be evaluated using a MicroFET® (Hoggan Health Industries, West Jordan, UT, USA) handheld dynamometer. Five measurements will be taken for each limb, of which the highest and lowest values will be discarded and the average between the three remaining values calculated [26].

##### Peripheral muscle endurance

The peripheral muscle endurance will be evaluated through the 30-s sit-to-stand test (30-STST) [27, 28]. The number of ≥ 2 repetitions in the test will be considered for analysis.

##### Functional capacity

Functional capacity will be evaluated by the six-minute walk test (6MWT) and the longest walk distance will be considered for analysis [29].

##### Health-related quality of life (HRQoL)

The HRQoL will be assessed using the Saint George's Respiratory Questionnaire [30].

##### Diaphragm and peripheral skeletal muscle architecture

Diaphragm and peripheral skeletal muscle architecture (cross-sectional area, muscle layer thickness and echogenicity) will be assessed with high-resolution US (Mindray Ultrasound, portable DP-2200, China), in B mode, with an echocardiologic transducer (65C15EA 5.0-9.0 MHz, 4W). The image analysis will be performed in ImageJ^®^ software (NIH, Bethesda, MD, USA) [31, 32].

##### Inflammatory biomarker

The hsCRP will be used as an inflammatory biomarker and calculated using standard method on a Mindray automated system (BS 380®, Shenzhen, China).

##### Endothelial function

The nitrate and nitrite levels will be used to assess endothelial function, on the Mindray automated system (BS 380®, Shenzhen, China), according to the modified Griess method by Tatsch et al. (2011) [33].

##### Oxidative stress

The oxidant profile will be analyzed by the Thiobarbituric Acid-Reactive Substances assay, advanced oxidation protein products, protein carbonylation test and the total oxidant status. The antioxidant profile will be measured by means of the total antioxidant capacity and the ferric reducing ability of plasma. The sample treatment will be based on established methods.

##### Muscular damage

Muscle damage will be evaluated by the Total creatine phosphokinase, lactate dehydrogenase and lactate that will be calculated using standard method on a Mindray automated system (BS 380®, Shenzhen, China).

##### DNA damage

The DNA damage will be measured by the comet assay and micronuclei analysis. We will select and analysis images of 100 cells from each sample according to tail length from 0 (no migration) to 4 (maximal migration), resulting in single DNA damage score (DNA damage index) [34]. Two different evaluators will analyze the slides under blind conditions [35]. Micronuclei analysis will be performed in peripheral blood lymphocytes as previously described [36].

### Participant timeline {13}

The participant timeline is shown in Table 1.

**Table 1 Tab1:** Participant timeline

	**STUDY PERIOD**			
	**Enrolment**	**Allocation**	**Post-allocation**	**Close-out**
**TIMEPOINT****	***-t***_***1***_	**0**	***t***_***1***_	***t***_***x***_
**ENROLMENT:**				
**Eligibility screen**	X			
**Informed consent**	X			
**Allocation**		X		
**INTERVENTIONS:**				
***IMT + NMES + PR group***			X	
***IMT + PR group***			X	
***NMES + PR group***			X	
***PR group***			X	
**ASSESSMENTS:**				
**Static and dynamic postural balance**	X			X
**Assessment of Fear of falling**	X			X
**Respiratory muscle strength**	X			X
**Inspiratory Muscle Endurance**	X			X
**Peripheral muscle strength**	X			X
**Peripheral muscle endurance**	X			X
**Functional capacity**	X			X
**Health-related quality of life**	X			X
**Laboratorial biomarkers**	X			X

### Sample size {14}

Based on the data from a previous study, performed by Mekki et al. [13] (*n*=45 participants, conducted in Tunisia), it will be necessary in a minimum sample size of 10 individuals per group and a total of 40 patients, considering the variable of mean lateral displacement of the pressure center mid-lateral displacement amplitude (COPml) in the follow-up of the intervention group, which performed NMES associated with PR program (±12.1 mm) and the control group that only performed standard PR (±7.2 mm). We also considered *p* value <0.05, power of 80% and loss of 20%.

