## Objectives {7}

Therefore, this study aims to investigate the effects of short-term multimodal exercise program (IMT plus NMES) compared to individualized addition of IMT or NMES to PR or standard PR on postural balance, fear of falling, muscle strength and endurance (peripheral and respiratory), functional capacity, HRQoL, muscle architecture (quadriceps and diaphragm), inflammatory profile, endothelial function, oxidative stress and DNA damage in patients with COPD. We hypothesize that the addition of a multimodal exercise program could potentiate the aforementioned outcomes.

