## Statistical methods

### Statistical methods for primary and secondary outcomes {20a}

The data will be analyzed using GraphPad Prism 5 (GraphPad Software Inc., San Diego, CA, USA). The normality of variables will be assessed by the Shapiro-Wilk test. The continuous variables with normal distribution and those with non-normal distribution will be presented as mean ± standard deviation (SD), 95% confidence interval (95% CI), and median (interquartile range), respectively, while categorical variables will be presented as absolute frequencies and percentages. Student’s *t* test for paired samples (parametric data) or Wilcoxon test (non-parametric data) will be used to compare the results before and after the intragroup intervention according to data distribution, and the effect size will be calculated using Cohen’s d. Comparison between groups will be performed using two-way analysis of variance (ANOVA) with repeated measures, followed by Bonferroni’s post hoc. Effect size was calculated using Cohen’s d. The significance level will be set at 5% (*p* <0.05).

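### The stated 80% power with 10 per group belongs to one unadjusted NMES+PR versus PR comparison, not to the multimodal question or the Bonferroni-adjusted test, and its inputs do not allow it to be reproduced

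*Protocol article*

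**What the plan says.** The section Sample size {14} of the protocol article states that "it will be necessary in a minimum sample size of 10 individuals per group and a total of 40 patients". The figures come from an earlier study and concern COPml at follow-up in the arm "which performed NMES associated with PR program (±12.1 mm) and the control group that only performed standard PR (±7.2 mm"). The remaining inputs are a p "value <0.05, power of 80% and loss of 20" per cent. The section mentions no contrast involving the multimodal arm, no four-arm test and no adjustment for multiple comparisons.

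Objectives {7} sets a different question: the multimodal programme "compared to individualized addition of IMT or NMES to PR or standard PR on postural balance". This gives three multimodal contrasts, within a four-arm 1:1:1:1 superiority design (Trial design {8}).

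Statistical methods {20a} compares the groups by two-way analysis of variance ("ANOVA) with repeated measures, followed by Bonferroni’s post hoc", at an overall 5% level. The number of comparisons that Bonferroni covers is not given. Section {20b} adds a baseline-adjusted ANCOVA, as a supportive analysis only. Outcomes are measured at baseline and after 8 weeks (Outcomes {12}).

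**The concern.** A power statement is specific to a contrast, an effect, a variance and a test. Here the contrast used for sizing does not include the multimodal arm, and the significance level used for sizing is looser than the one the post hoc test will apply to each comparison. In addition, a two-sample calculation needs both a mean difference and an SD, and only one pair of figures is reported.

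What is at stake is how a non-significant result is read. The stated hypothesis is that the combination potentiates the outcomes, and the Discussion looks to the adoption of new rehabilitation models. A reader who takes the 80% as applying to multimodal versus a single add-on may read non-significance as absence of added benefit, although power for that contrast was never established.

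**Working it through.** **Inputs.** From Sample size {14}: 10 per group, alpha 0.05, power 80%, loss 20%, and the figures 12.1 and 7.2 mm. From Objectives {7}: three multimodal contrasts; four arms give 4×3/2 = 6 pairs. Assumed: two-sided tests (sidedness is not stated) and equal variances.

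**Attempt to reproduce 10 per group.** Evaluable per arm after loss: 10 × 0.8 = 8. The standardised difference d = (mean difference)/SD cannot be formed, because one of its two parts is missing. The figure is therefore not reproducible from the stated inputs. What can be done is to solve backwards for d.

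- Two-sample t-test, n = 8 per arm, df = 14, noncentrality d√(n/2) = 2d. Power is 80% at d = 1.507 (normal approximation: 1.40).
- If the ± figures are SDs: root-mean-square SD = √((12.1² + 7.2²)/2) = 9.96 mm, so the implied difference is 1.507 × 9.96 = 15.0 mm. That difference is not in the article.
- If they are means: difference = 12.1 − 7.2 = 4.9 mm, so the implied SD is 4.9/1.507 = 3.25 mm, about 3.3. That SD is not in the article. On this reading the NMES arm would also have the larger sway amplitude at follow-up, which sits awkwardly with the Discussion's statement that NMES added to rehabilitation improves static balance.
- If 10 rather than 8 are evaluable: d = 1.325, which is 13.2 mm or an SD of 3.70 mm.

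**Effect of Bonferroni at the same d = 1.507, n = 8 per arm, follow-up-only t-test.** Noncentrality = 2 × 1.507 = 3.01; per-comparison alpha = 0.05/k.

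| Comparisons k | Alpha | Power, two-arm df (14) | Power, pooled df (28) |
|---|---|---|---|
| 1 | 0.05 | 80% (by construction) | 83% |
| 3 | 0.0167 | 62% | 68% |
| 6 | 0.0083 | 50% | 57% |

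The columns must be read separately: 80% falls to 62% or 50%, and 83% falls to 68% or 57%. With 10 evaluable per arm and d = 1.325, the six-pair figures are 52% and 57%, so the drop does not depend on how the 20% loss is treated.

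**Sensitivity to the planned test.** The repeated-measures analysis uses baseline as well. Let ρ be the correlation between baseline and week 8, which the article does not give, and keep d = 1.507 on the follow-up SD. The group-by-time contrast then has effect d/√(2(1−ρ)), and ANCOVA has d/√(1−ρ²). Six-pair Bonferroni, 8 per arm, pooled df:

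| Assumed ρ | Change from baseline | ANCOVA |
|---|---|---|
| 0.3 | 40% | 62% |
| 0.5 | 57% | 73% |
| 0.6 | 70% | 81% |
| 0.7 | 84% | 90% |

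Power can thus fall on either side of 80%.

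**Which contrast the planning effect speaks to.** If the effects of IMT and NMES simply add, then (IMT+NMES+PR) − (IMT+PR) equals the NMES effect, which is the planning contrast. Multimodal minus PR would be the sum of the two effects. Multimodal minus NMES+PR would be the IMT increment, for which no figure is given. Additivity is itself an assumption; the article states no effect size for any of the three.

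**The case against.** The strongest case on the other side has four parts.

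- The article openly names NMES+PR versus PR as the basis of the calculation and does not say that 80% holds for every contrast. This stands. The defect is that no power is stated for the question the trial asks, while "power of 80% and loss of 20" per cent is the only power statement there is.
- The reduced powers rest on an effect solved backwards from 80%, on a follow-up-only t-test, and on a number of comparisons the article does not fix. This also stands, so they are given as a conditional range. A single figure such as 57% should not be written into the protocol.
- A condensed article may leave full inputs to the full protocol, and the mean difference may be in the cited study. This explains the gap in part. But the article chose to report the calculation, and gave two ± figures that cannot be identified as means or SDs.
- Recruitment is over and the trial status is completed, so the sample size cannot change. True; the correction concerns interpretation only.

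Two stronger readings are tempting. A reader might infer that differences from the single add-on arms must be smaller than the planning effect, because those arms already contain part of the combination. The documents do not support this: under additivity, multimodal versus IMT+PR equals the planning effect, and the stated hypothesis is potentiation. A reader might also infer that the trial is not powered for multimodal versus IMT+PR or NMES+PR. The documents give no effect for either, so the most that can be said is that power for them was not established.

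**Conclusion.** The point holds as a mismatch and a reporting defect. The 80% attaches to one unadjusted two-arm comparison of COPml that does not involve the multimodal arm, and 10 per group cannot be reproduced from what is stated. No arithmetic slip is shown, because the arithmetic cannot be checked.

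The size is conditional. With 8 evaluable per arm, two-sided testing and a back-solved d of about 1.5, Bonferroni brings a follow-up-only t-test to 62% (three contrasts) or 50% (six pairs) with two-arm df, or to 68% or 57%, against 83% unadjusted, with df pooled over four arms. The power of the planned repeated-measures test could be lower or higher than these. The mismatch itself depends on none of these assumptions: it follows from setting the sample size section beside the objectives and the statistical methods. It should be corrected before results are interpreted against the stated power.

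**What to change.** Keep N=40 and revise the text as follows.

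1. State that the 80% applies only to one unadjusted NMES+PR versus PR comparison of COPml.
2. State whether 12.1 and 7.2 mm are means or SDs, and give the missing mean difference or SD.
3. State how many comparisons Bonferroni covers, and give the resulting power as a range conditional on the assumed effect, degrees of freedom and baseline correlation.
4. State that no effect was planned for the multimodal contrasts, so power for them was not established. Add that under additivity multimodal versus IMT+PR would equal the planning effect, while the IMT increment over NMES+PR has no planning figure.
5. Report all three multimodal contrasts as differences with confidence intervals, and do not read non-significance as no added benefit.

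The cost is a change of text: no further patients and no new data. The downside is that the stated power becomes less favourable.

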### Recruitment {15}

Patients will be recruited from the waiting list for the PR program at the outpatient pulmonology clinic of the University Hospital of Santa Maria, Rio Grande do Sul, Brazil.

## Assignment of interventions: allocation

### Sequence generation {16a}

A computer-generated list of random numbers will be used, and a randomization sequence will be created using the Random Number Generator Pro v2.00 software (Segobit, Issaquah, WA, USA).

### Concealment mechanism {16b}

A single investigator blinded to patient identity ([name]) will randomly divide patients into the four groups (1:1:1:1): the multimodal exercise program (IMT + NMES + PR group), (IMT + PR group), (NMES + PR group), or standard PR group.

### Implementation {16c}

All eligible patients who provide consent for participation and fulfill the inclusion criteria will undergo an initial study evaluation. Immediately after the initial assessments, the project manager ([name]) will complete the randomization and reveal the group allocation to the patient and physiotherapist responsible for performing the intervention protocols. Randomization will be conducted without any influence of the principal investigators, outcome assessors, or physiotherapists. Assessments will be conducted by independent assessors, blinded to group allocation. All data analyses will be blinded.

## Assignment of interventions: blinding

### Who will be blinded {17a}

This will be a single-blind study, in which the outcome assessors will have no information regarding the study group.

### Procedure for unblinding if needed {17b}

The design is open-label with only outcome assessors being blinded so unblinding will not occur.

## Data collection and management

### Plans for assessment and collection of outcomes {18a}

As previously described (item outcomes - 12), all assessments will be performed using instruments previously validated in the literature. At least three measurements will be performed for the performance tests. The evaluators will be physical therapists with at least 1 year of training experience in the evaluation instruments used in this study.

### Plans to promote participant retention and complete follow-up {18b}

The participants who enroll in the study in each session will be asked to provide feedback regarding their health status. Participants will receive a schedule with the dates and times for the assessment and training, in addition to a text message to remind them of the training schedule. An intention-to-treat analysis will be applied to include all randomized participants.

### Data management {19}

After inclusion, a unique identification code will be assigned to each participant. An Excel file including the individual codes and the corresponding participants will be stored by a leading researcher ([name]). All data collected/analyzed will be entered into an anonymized/coded Excel database. Consents and printed documents will be stored for 5 years after the end of the study and will be discarded thereafter.

### Confidentiality {27}

All laboratory specimens and data collection forms will be identified using coded ID numbers to maintain the participants’ confidentiality. None of the personal information of potential or enrolled participants will be shared or released.

### Plans for collection, laboratory evaluation and storage of biological specimens for genetic or molecular analysis in this trial/future use {33}

Blood samples will be collected after an 8-h overnight fast. Serum will be used for the analysis of high-sensitivity C-reactive protein (hsCRP), total antioxidant capacity, total oxidant status, nitrate and nitrite, creatine phosphokinase, and lactate dehydrogenase levels. Plasma will be used to assess the advanced oxidation protein products, the ferric reducing ability of plasma, Thiobarbituric Acid-Reactive Substances assay, protein carbonylation, DNA damage, and musculature. Biological samples will be stored at the Research Laboratories of Clinical Biochemistry and Biogenomics at “X”.

## Statistical methods

### Statistical methods for primary and secondary outcomes {20a}

The data will be analyzed using GraphPad Prism 5 (GraphPad Software Inc., San Diego, CA, USA). The normality of variables will be assessed by the Shapiro-Wilk test. The continuous variables with normal distribution and those with non-normal distribution will be presented as mean ± standard deviation (SD), 95% confidence interval (95% CI), and median (interquartile range), respectively, while categorical variables will be presented as absolute frequencies and percentages. Student’s *t* test for paired samples (parametric data) or Wilcoxon test (non-parametric data) will be used to compare the results before and after the intragroup intervention according to data distribution, and the effect size will be calculated using Cohen’s d. Comparison between groups will be performed using two-way analysis of variance (ANOVA) with repeated measures, followed by Bonferroni’s post hoc. Effect size was calculated using Cohen’s d. The significance level will be set at 5% (*p* <0.05).

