#### Primary outcome

##### Static postural balance

The primary outcome will be measured using the AMTI portable force platform model OR6-6-2000 (Advanced Mechanical Technologies, Inc.) with an acquisition frequency of 100 Hz [17]. Standardized verbal instructions will be used to guide proper patient positioning. Three attempts lasting 30 seconds each, with 1 minute rest in between, will be performed (eyes open and then closed) and the average will be considered for analysis [18].

Body sway will be evaluated from the center of pressure (COP) and the variables will comprise COP anteroposterior displacement amplitude (COPap), COP mid-lateral displacement amplitude (COPml), COP displacement velocity (COPvel) and 95% ellipse area (AE). Then, the raw data obtained will be filtered using a fourth-order zero-lag Butterworth with 10 Hz cut-off frequency, and processed using custom Matlab routines (R2020a, The Mathworks, Inc., Massachusetts, USA).

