### Methods for additional analyses (e.g. subgroup analyses) {20b}

We will use analysis of covariance (ANCOVA), as a supportive analysis, to compare differences between groups after the intervention, adjusting for values of the respective outcomes at baseline.

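### The between-arm ANOVA has no stated route for skewed outcomes: it stays valid, but could lose substantial power if sway or biomarker variables are right-skewed

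*Protocol article*

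**What the plan says.** Section {20a} of the Protocol article begins with a distributional screen: "The normality of variables will be assessed by the Shapiro-Wilk test". The result decides two things. One is the summary: mean with SD, or median with interquartile range. The other is the pre-post test inside each arm: a paired t test, "or Wilcoxon test (non-parametric data) will be used to compare the results before and after the intragroup intervention according to data distribution".

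The next rule has no such branch: "Comparison between groups will be performed using two-way analysis of variance (ANOVA) with repeated measures", with Bonferroni post hoc tests. No transformation and no rank-based alternative is named for it.

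The section on additional analyses {20b} adds an ANCOVA "as a supportive analysis, to compare differences between groups after the intervention, adjusting for values of the respective outcomes at baseline". It is also parametric, with no transformation stated.

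The section Trial design {8} calls this a four-arm superiority study with equal allocation, so the between-arm comparison is the one that answers the trial's question.

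**The concern.** The plan foresees non-normal outcomes but provides for them only in the secondary, within-arm comparison. An outcome judged non-normal would be described by medians, tested within arms by ranks, and compared between arms by means.

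Several outcomes are strictly positive and could be right-skewed. Among the primary sway variables these are the 95% ellipse area and sway velocity; among the biomarkers they include hsCRP and creatine phosphokinase. If they are skewed, an ANOVA on change in raw units is dominated by the few patients with large values. A trial of 40 patients in four arms has little power to spare.

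A separate and smaller matter is the screen itself. If it is applied arm by arm, a normality test on about 10 values is unreliable.

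**Working it through.** **Inputs from the Protocol article.** Four arms, 1:1:1:1 (Trial design {8}); 10 per arm, 40 in total, with 20% loss allowed (Sample size {14}), so 10 × (1 - 0.2) = 8 per arm if that loss occurs; 5% significance level ({20a}). The plan gives no figure on this point to reproduce. The sample-size statement cannot be rebuilt because it does not give both a difference and an SD, but nothing below depends on it.

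**Assumptions.** Lognormal outcomes with log-SD s = 0.4, 0.6 or 0.8. The coefficient of variation is √(exp(s²) - 1), which gives 42%, 66% and 95%. Pre-post correlation is 0.6. Arm effects on the log scale are δ = -1.2, -0.6, -0.6 and 0 SD.

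**Model.** With x and e independent standard normal, y = 0.6x + 0.8e + δ, where 0.8 = √(1 - 0.6²). Baseline is exp(s·x) and follow-up is exp(s·y).

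**Tests.** With two time points, the group-by-time F of the repeated-measures ANOVA equals a one-way ANOVA F on change, with 3 and 40 - 4 = 36 df. The ANCOVA F for arm has 3 and 40 - 5 = 35 df. These are omnibus powers, not powers for the Bonferroni pairwise comparisons.

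**Power, 10 per arm.**

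| Log-SD | RM-ANOVA raw | RM-ANOVA log | ANCOVA raw | ANCOVA log |
|---|---|---|---|---|
| 0.4 | 47% | 65-68% | 71% | about 76% |
| 0.6 | 35% | 65-68% | 63% | about 76% |
| 0.8 | 28% | 65-68% | 53% | about 76% |

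A separate run of 4,000 trials per setting (Monte Carlo standard error at most √(0.25/4000) = 0.8 points) used log-SD 0.5 / 0.8 / 1.0. RM-ANOVA gave 40% / 26% / 20% raw against 65% / 66% / 67% on logs. With 8 per arm it gave 34% / 20% / 16% against 54% / 53% / 52%.

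**Type I error.** In that run the raw RM-ANOVA rejected in 3.8% to 5.0% of null trials under skew at 10 per arm. Across all the simulations the range is about 3% to 6%.

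**Where the loss comes from.** Moving from raw RM-ANOVA to raw ANCOVA gains 71 - 47 = 24 points at log-SD 0.4 and 53 - 28 = 25 points at 0.8. Moving from raw to log ANCOVA then gains 76 - 71 = 5 and 76 - 53 = 23 points. With normal data, baseline adjustment alone gains 76 - 67 = 9 points. At mild skew most of the recoverable power is therefore baseline adjustment; at strong skew the scale matters about as much.

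**Copying the rank route across does little.** Kruskal-Wallis on change gives 42% / 35% / 33% at log-SD 0.5 / 0.8 / 1.0, against 40% / 26% / 20% for raw RM-ANOVA. Rank ANCOVA gives 71% at all three.

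**Little skew.** At log-SD 0.2, in a two-arm model with 8 per arm and a 1.2 log-SD effect, ANCOVA has 76% raw against 77% log, and the change-score test 64% against 72%.

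**The screen.** If run on each arm of 10, Shapiro-Wilk detects the skew in a proportion p of about 20% / 32% / 47% of samples. The chance that four equally skewed arms do not all get the same verdict is 1 - p⁴ - (1 - p)⁴. For p = 0.20 this is 1 - 0.002 - 0.410 = 59%; for 0.32 and 0.47 it is 78% and 87%. If run on 40 pooled values, it detects the skew in about 70% / 93% / 99.6%, and arms cannot diverge.

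**The case against.** The strongest reply is that the between-arm test is fixed in advance, which is normally what a statistician wants, and that it controls type I error. That stands. A reader might infer from the Shapiro-Wilk step that chance decides which test answers the superiority question. The text does not support this: the screen governs only summaries and within-arm tests, so the divergent-verdict figures say nothing about between-arm power. A reader might also infer a risk of false positives; the simulations show none of note.

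Second, two premises are inferred. Raw-scale analysis is read from the absence of any stated transformation, and arm-by-arm screening from the intragroup use of the result. Both are reasonable readings, but neither is written. Transformation details may also sit in a full protocol or SAP that is not shown. What remains is a contrast within the article itself: a distribution-dependent rule for one comparison and an unconditional rule for the more important one.

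Third, the size is driven by assumption. Lognormal data with effects set on the log scale favour a log analysis by construction, and nothing shows that COPml, the variable used for the sample size, is skewed. This also stands, and is why the figures are given as a range that includes little skew.

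Fourth, part of the loss is change-score analysis against ANCOVA, and {20b} already plans the ANCOVA. That is correct, but it is only supportive there, and on raw values it softens the loss under skew without removing it.

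**Conclusion.** The point holds as one of efficiency and coherence, not validity. The planned ANOVA is a legitimate test. If the skew-prone outcomes have log-SD of 0.4 to 0.8, it gives up roughly 20 to 40 points of omnibus power against the same ANOVA on logs (for example 65 - 47 = 18 and 68 - 28 = 40), and more against a log-scale ANCOVA. If outcomes are near normal there is no loss from the scale, and ANCOVA is barely affected at log-SD 0.2 or below. All of this rests on the assumed lognormal shape, correlation of 0.6 and effect pattern, since the protocol gives no distribution data. The weakness of the Shapiro-Wilk screen is a separate, lesser matter confined to descriptive summaries and within-arm tests, and it depends on the screen being run per arm.

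**What to change.** Make the baseline-adjusted ANCOVA already described in {20b} the main between-arm analysis. Drop the Shapiro-Wilk gate. Set the scale per outcome without reference to treatment effects: natural log for strictly positive, skew-prone sway and biomarker variables; raw for scores, distances and pressures. Check the residuals of the fitted model, and treat within-arm tests as descriptive only.

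The Trial status section lists the trial as completed, so this cannot be presented as fixed before the data were collected. The report should state when the scale was chosen, and show the planned repeated-measures ANOVA on raw values alongside.

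The cost is analysis and wording only, with no new patients or measurements. The downside is that logged effects read as ratios rather than in the original units, so raw mean differences should be shown too.
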